### Participant recruitment and informed consent

Data collection will begin in October 2022 and is expected to end in September 2023. Shenzhen People’s Hospital is the pilot research unit, and the pilot research will be carried out from August to September 2022. The annual census of very preterm infants in this facility is relatively high and the breastfeeding rate is very high (above 80%), hence ideal for the recruitment of subjects. Mothers who meet the inclusion criteria (fetal weight < 1500 g estimated by ultrasound) will be invited to participate. To achieve full registration of participants and target sample size, breast-feeding education will be provided in obstetrics to improve lactation awareness. Professional staff will guide pregnant women and provide them with breast care (such as breast massage). The principal investigator (PI) will explain the study in detail and respond to any questions raised. Mothers will be informed of their right to withdraw from the intervention at any time. They will also be informed that if they decline to participate in the study, their care and that of their infants will not be affected.

Written informed consent will be obtained from the patient's guardian. This study complies with the Declaration of Helsinki.

### Randomization

A 1:1 block randomization scheme will be adopted. Each group will be stratified by birth gestational age (< 28 weeks, 28 weeks, and 32 weeks). A random serial number will be randomly generated for each layer using SAS (v9.4 SAS Inst. Inc., Cary, NC) before the start of the study. The block length will be 6. Statisticians will prepare sealed, numbered, opaque envelopes for each site and hand them over to the study coordinator, who will ensure that the envelopes are used in a numerical order. After receiving the notice, the study coordinator will open the envelope, take down the group assignment form, copy the form and send it to the statistician. The manuscript will be left in the case file of the preterm infant. To achieve blinding, the study coordinator preparing the syringe (colostrum or placebo) will be different from the nurse conducting the intervention. The subjects, intervention nurses, the principal investigator and the data verifier will be blinded. During the pilot test, non-fixed codes will be used for blinding to represent each allocation scheme to prevent unblinding by inadvertently losing blindness to all trial participants.

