### Inclusion/exclusion criteria

Inclusion criteria: 1. gestational age less than 32 weeks and birth weight less than 1500 g; 2. admission to NICU ≤ 24 h; and 3. be able to start the agreement within 72 h of birth.

Exclusion criteria: 1. birth asphyxia (defined as umbilical artery / first hour arterial PH < 7.0 or cardiopulmonary resuscitation in the delivery room); 2. birth complicated by severe gastrointestinal malformations (such as intestinal atresia, esophago-tracheal fistula, intestinal rotation abnormalities, congenital megacolon); 3. prenatal diagnosis of congenital chromosomal abnormalities or suspected congenital genetic metabolic diseases; and 4. maternal drug abuse or contraindications to breastfeeding (HIV and cytomegalovirus infection).

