### Trial status

This is a current, ongoing trial which is actively recruiting study participants. We expect to finish patient recruitment in September 2023 and will present the final results during 2024.

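### A single published block length of 6 lets anyone who knows the earlier allocations foresee up to a quarter of assignments: an avoidable weakness in concealment, not demonstrated selection bias

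*Protocol article*

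**What the plan says.** All of the allocation method is in the protocol article, Randomization.

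- **Method:** "A 1:1 block randomization scheme will be adopted", and "The block length will be 6". No variation in block length is mentioned.
- **Lists:** "Each group will be stratified by birth gestational age (< 28 weeks, 28 weeks, and 32 weeks"), and "A random serial number will be randomly generated for each layer using SAS". Site is not named as a stratification factor, but "Statisticians will prepare sealed, numbered, opaque envelopes for each site and hand them over to the study coordinator".
- **Who sees allocations:** once notified, "the study coordinator will open the envelope, take down the group assignment form, copy the form and send it to the statistician". The coordinator also prepares the syringes and is not among the roles listed as blinded. What appears to be the original of the form stays in the infant's file.
- **Protections:** envelopes are sealed, opaque, numbered and used in order. The intervention nurses and the principal investigator are listed as blinded.

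Three other sections bear on the point. The collection and administration section describes the person preparing syringes as an on-site investigator. Inclusion/exclusion criteria requires that an infant "be able to start the agreement within 72 h of birth", without defining this further. Trial status says: "This is a current, ongoing trial which is actively recruiting study participants".

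**The concern.** Sealed envelopes conceal the next allocation only if it cannot be worked out from the previous ones. With one known block length, a person who has followed a list knows where each block ends. Once one arm has used its three places, every remaining place in that block belongs to the other arm. Publishing the length during recruitment means that this person does not have to infer it.

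At stake is the comparability of the arms. If foreknowledge ever reached a person who influences whether or when an infant is enrolled, the arms could come to differ in prognosis. Factors that the Discussion names as shaping gut microbiota, such as feeding type and antibiotic exposure, could then be unbalanced. The primary analysis is planned around a modest difference (0.2 on a standard deviation of 0.6), so it has limited tolerance for such an imbalance.

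**Working it through.** **The plan's own figure.** The article gives no figure for predictability. The figure used here is the total of 320 (Sample size), which can be reproduced. With difference 0.2, SD 0.6, two-sided 0.05 and 80% power, the normal approximation gives n = 2 × (1.960 + 0.842)² × (0.6/0.2)² ≈ 141.3, rounded up to 142. The t-test solution is 142.2, rounded up to the stated 143. Inflating by n/(1 − d) gives 159 per arm at 10% loss and 163 at 12%. The stated 160 corresponds to a loss of 1 − 143/160 = 10.6%. Block length enters none of these.

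**Certain assignments in a block of six.** There are C(6,3) = 20 equally likely blocks. An assignment is certain once one arm has used its three places.

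| Position | Condition for certainty | Probability |
|---|---|---|
| 1 to 3 | not possible | 0 |
| 4 | first three all in one arm | 2/20 = 0.10 |
| 5 | first four split 3:1 | 8/20 = 0.40 |
| 6 | always | 1.00 |

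The sum is 1.5 per block, and 1.5/6 = 25%. For 320 infants, 0.25 × 320 = 80.

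**Best guess.** Always guessing the arm with more places left is right with probability 0.5, 0.6, 0.6, 0.7, 0.7 and 1.0 at positions 1 to 6. The sum is 4.1, and 4.1/6 = 68.3%, against 50% by chance.

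**Unfinished last blocks.** The article does not settle how many lists there are, so 320 infants were simulated over 2, 3, 6 and 9 separate lists, with equal expected sizes as an assumption. The mean certain share was 24.6%, 24.5%, 24.1% and 23.5%. In any one trial the share varies by chance: the central 95% of simulated trials ran from about 22% to 28% with 2 lists, and from about 21% to 27% with 9. So 25% is the ceiling for the expected share, not for each realisation.

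**Effect of varying the block length.** The simulation assumed an observer who knows all earlier allocations and the set of possible sizes, but not their order. The sizes are illustrative and do not come from the article.

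| Block lengths | Certain assignments | Best guess correct |
|---|---|---|
| 6 only | 25% | 68% |
| 4 and 6 | about 6% | about 69% |
| 4, 6 and 8 | about 2% | about 68% |

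Varying the length removes nearly all certainty but hardly changes how often a good guess succeeds.

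**The case against.** The strongest counter-argument is that selection bias needs one person who can both foresee the next arm and influence entry, and the article separates these roles. The coordinator sees allocations but is given no part in eligibility or consent. The principal investigator explains the study to mothers and is listed as blinded. The envelope is opened only after notification, so someone else triggers enrolment. Staff who do not know past allocations learn nothing useful from the block length. A fixed block of six with sequential opaque envelopes is also a common design.

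Most of this stands, and it rules out three stronger readings that a reader might infer.

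- **That the coordinator can steer enrolment.** No section gives the coordinator that power.
- **That the 72-hour criterion turns on the infant's stability or the mother's milk supply.** Neither is listed under entry. Instability appears as a reason to interrupt treatment, and a minimum milk volume appears under milk collection. That the criterion leaves room for judgement is an inference from its being undefined.
- **That 80 infants will have a foreseeable assignment.** This needs an observer who sees every allocation in a list. If blocks run across sites, someone at one site sees only part of each block and can predict less. The article does not say which applies.

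The role separation is nevertheless not watertight. The syringe preparer is on site, and the form in the infant's file is not stated to be restricted to the coordinator. Under Quality control, the site principal investigators sit on the data monitoring committee, which has unblinded access to data at the interim analysis. If recruitment is still open then, someone who talks to mothers may know past allocations.

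**Conclusion.** The point holds as a minor, avoidable weakness in concealment. The article fixes one block length and made it public during enrolment. A person who knows all earlier allocations in a list can be certain of up to 25% of later ones on average (at most about 80 of 320 in expectation) and can guess correctly 68.3% of the time.

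This rests on complete 3:3 blocks and full knowledge of the list. It falls to about 23.5% with nine lists, and lower still for a single-site observer if blocks span sites. The article does not show that a person with this knowledge decides entry, and gives no basis for saying how often foreknowledge would be acted on. Selection bias is therefore not demonstrated, and nothing here invalidates the randomization already carried out.

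**What to change.** Three changes, the first for envelopes not yet issued:

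1. Regenerate the remaining lists with randomly varying block lengths (for example 4, 6 and 8) that are not disclosed to sites or given in any public document. State whether blocks run within or across sites, and set out how part-filled blocks are handled at the switch.
2. Record eligibility irrevocably, including the 72-hour criterion, before the coordinator is notified. This is needed because varied blocks leave the guess rate near 68%. It formalises the order that the article already implies.
3. Keep the assignment form out of the infant's file, in a place closed to blinded staff.

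**Cost:** retrieving and replacing unissued envelopes at three sites, a protocol modification submitted to the ethics committee, and slightly looser balance within strata at any moment. The sample size does not change.

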### Collection of milk and oropharyngeal administration procedure

Obstetric nurses will encourage the mother of each newborn to start lactation within 24 h of delivery and educate them on breast massage and electric breast suction every 3 h. Mothers of preterm infants will be encouraged to milk frequently with hygienic hands to ensure a steady supply of breast milk. To ensure the feasibility of oropharyngeal administration of mother’s milk to preterm infants in the treatment group, the mother’s milk will be collected in a pre-labeled sterile milk collection bag. A minimum colostrum volume of 1.6 ml will be collected and stored in the breast milk refrigerator of NICU. After ascertaining that baby's information is consistent with details in the label on the breast milk storage bag, an on-site investigator (nurses preparing syringes) will select the storage bag with the latest lactation time and use sterile gloves and syringes to suck 0.1 ml of colostrum or sterile water for oropharyngeal administration, and cover them with opaque tape and needle cap. Each syringe will be labeled with serial number, hospitalization number, name and date. Then, the bag will be stored at 0 ~ 4℃ for 24 h for subsequent intervention. In this study, all other storage bags will be stored in a freezer at -18 °C until the infant begins enteral feeding.

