In the first 48–72 h the treatment group will receive the treatment measures: two 1 mL sterile syringes each aspirated with 0.1 mL of colostrum, placed at room temperature for 5 min. The colostrum will be maintained at room temperature for OAC use. After removing the tip and cap of the first syringe, the colostrum will be slowly injected along the right oral mucosa for at least 20 s. Then, the right buccal mucosa will be wiped with a sterile cotton swab for at least 10 s. The second syringe will be used in the same way on the left oral mucosa. The procedure will be performed every three hours for five days. The control group will be treated with sterile water following similar operation steps. Colostrum for the control group will be frozen in the NICU breast milk refrigerator for enteral feeding. Vital signs will be monitored throughout the process, including heart rate, respiration, body temperature and pulse oxygen saturation. During treatment, newborns will be regularly monitored and observed. If their clinical symptoms are unstable (heart rate is greater than 200 or less than 100, breathing is greater than 80, or the oxygen saturation is maintained above 85% only when the oxygen concentration increases by 10%) [44], the intervention will be interrupted. Once the clinical situation stabilizes, the treatment will be resumed immediately, and the final intervention dose and adverse reactions recorded.

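### The intervention nurses are declared blinded, but the described masking stops at the syringe and nothing described hides the liquid at delivery or on the swab

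*Protocol article*

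**What the plan says.** The Randomization section makes the blinding claim without qualification: "The subjects, intervention nurses, the principal investigator and the data verifier will be blinded". It supports the claim by separating two tasks: "the study coordinator preparing the syringe (colostrum or placebo) will be different from the nurse conducting the intervention".

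The section on milk collection and oropharyngeal administration adds physical masking. Whoever draws up the colostrum or water is to "cover them with opaque tape and needle cap".

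The same section then sets out the bedside steps. There are "two 1 mL sterile syringes each aspirated with 0.1 mL of colostrum", with sterile water given to controls by similar steps. Delivery begins "After removing the tip and cap of the first syringe", after which "the colostrum will be slowly injected along the right oral mucosa for at least 20 s" and "the right buccal mucosa will be wiped with a sterile cotton swab for at least 10 s". The left side is treated in the same way, and the whole procedure is repeated three-hourly for five days.

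Three other places bear on the consequences:

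- The administration section sets vital-sign limits for interrupting the intervention, and has it resumed once the infant's condition is stable.
- Missing data counts an infant as lost to follow-up if the dose received falls short of 70% of that intended, or if the study is not continued because of unstable symptoms.
- Quality control defines adverse events partly by their relation to the intervention or to fresh breast milk, and gives the data monitoring committee (DMC) the task of verifying how well the blinding works.

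**The concern.** The masking protects two stages: preparing the syringe and the liquid inside the barrel. The blinding claim covers a third stage, delivery, at which the cap is off and the liquid is in the infant's mouth and then on cotton. No colouring, appearance-matched placebo, screen or other device is described for that stage. Covering the syringe with opaque tape makes sense only if the contents might be recognised, so the plan itself treats appearance as a possible route of unblinding and then leaves that route open at the point of use.

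At stake is the credibility of anything recorded or decided at the cot. A nurse who knows the arm might be quicker or slower to withhold or resume a dose, or might describe an event after a dose differently. Those records feed the safety review and the dose threshold that decides who counts as lost. A report calling the trial double-blind would credit these data with a protection that the procedure does not show.

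**Working it through.** **Inputs (Protocol article, administration section unless stated).** One procedure every 3 h for 5 days; 2 syringes of 0.1 mL per procedure; at least 20 s of injection and at least 10 s of swabbing per side; minimum colostrum collection 1.6 mL; 70% dose threshold (Missing data).

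**Check of the schedule against the plan's own figure.** Procedures per day = 24 / 3 = 8. Daily volume = 8 × 2 × 0.1 mL = 1.6 mL, which equals the stated minimum collection volume. The schedule has therefore been read correctly.

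**Exposure per infant, if no dose is missed.**
- Procedures: 8 × 5 = 40.
- Syringe deliveries: 40 × 2 = 80, with 80 swabbings.
- Time with the liquid outside the syringe: 80 × (20 + 10) s = 2,400 s = 40 min, as a minimum.
- At the 70% threshold: 0.7 × 40 = 28 procedures, or 56 deliveries.

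These counts are per infant. The article does not say how many nurses share them.

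**Does the described masking reach each stage?**

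| Stage | Described protection |
|---|---|
| Drawing up | Different person from the nurse giving the dose |
| Liquid in the barrel | Opaque tape and cap |
| Liquid leaving the uncapped tip | None described |
| Liquid on the mucosa | None described |
| Liquid on the swab | None described |

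**How recognisable would the liquid need to be?** The article does not describe how either liquid looks, so this is an assumption shown over a range. Let q be the chance that one delivery reveals the liquid to whoever gives it, treating deliveries as independent. The chance of at least one reveal in n deliveries is 1 − (1 − q)^n.

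| q | n = 80 | n = 56 |
|---|---|---|
| 1% | 55% | 43% |
| 2% | 80% | 68% |
| 5% | 98% | 94% |
| 10% | >99.9% | 99.7% |

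This is an illustration only, since independence is unlikely to hold exactly. It shows that with this many repetitions, recognition need not be easy on any single occasion for the blinding to be at risk.

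**Route to the data.** An infant falls below 70% when at most 27 of 40 procedures are given, that is, when 40 − 27 = 13 or more are withheld. Knowledge of the arm that altered how readily doses were withheld or resumed could thus move an infant across the line into follow-up loss.

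**The case against.** The strongest reply has four parts.

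- **Appearance is undocumented.** Nothing in the article says that the liquids look different in use. The volume is 0.1 mL over at least 20 s, at most 0.1 / 20 = 0.005 mL per second, in the mouth of an infant under 1500 g. The text prescribes injecting and wiping, not watching. This stands. It rules out the stronger reading that a reader might infer, namely that bedside blinding does not exist, or that the nurses of essentially all 320 infants know the arm after the first dose or so. The documents support only that blinding is not secured.
- **There are other safeguards.** The preparer is a different person, and the DMC is to verify the blinding. Both are real and should be credited, but neither hides the liquid at delivery. The article is condensed, and a fuller document may describe a further measure. The point does not rest on that silence alone: the article sets out its masking and its bedside steps in detail, and the two together do not deliver the stated claim.
- **No entry is assigned to this nurse.** The article does not say who records interruptions, doses or adverse events, and the limits for interruption are numeric. This stands as far as it goes: the route to bias is possible, not documented. Some judgement remains, because resumption depends on the infant being considered stable, Quality control speaks of unstable vital signs without figures, and linking a cytomegalovirus infection to fresh milk requires attribution.
- **The outcomes are laboratory measures.** All listed primary and secondary outcomes come from sequencing or LC–MS. This stands for the assays. It does not cover which infants are retained, given the 70% rule.

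**Conclusion.** The statement that intervention nurses are blinded is wrong as written, because the described procedure does not secure it. The gap recurs up to 80 times per infant, for at least 40 minutes in total. The conclusion rests on one reasonable but undocumented assumption: that colostrum can be told from sterile water at the syringe tip, in the mouth or on a swab.

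The consequence is limited. The assays behind the primary and secondary outcomes are not affected. Dose interruption, the dose count against the 70% rule and adverse-event attribution could be influenced by knowledge of the arm, but the documents give no basis for putting a size on that influence. The point concerns the nurse giving the dose. It does not by itself show that parents, the principal investigator or the data verifier are unblinded.

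**What to change.** In Randomization, either state the measure that masks the liquid at delivery, or describe the intervention nurse as potentially unblinded and confine the blinding claim to roles the procedure can blind. In addition:

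- Log interruptions from the monitor read-out against the limits already in the administration section, so that the dose count used for the 70% rule does not depend on the nurse's judgement.
- Have adverse events classified by an existing team member whose blinding is documented and who cannot see the allocation form. Treating physicians are not among the roles listed as blinded, and Randomization leaves that form in the infant's case file. The principal investigators and data verifiers are listed as blinded but sit on the DMC, which Quality control gives unblinded access to the data, so the choice has to allow for that too.
- Discard used syringes and swabs out of sight of other staff and parents.
- Record the nurse's guess of allocation, as part of the check on blinding that Quality control already assigns to the DMC.

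The cost is protocol wording, reassignment of a few existing entries, one extra item to record and a change in waste handling. The sample size does not change. The downside is that the trial can no longer claim that the person giving the treatment was blinded.

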### Data collection

Descriptive and clinical data be collected from both groups. Birth status characteristics, such as delivery mode, gestational age, weight and length, Apgar score will be collected in addition to the mothers’ occupation, education level, disease, use of drugs, supplements and antibiotics. During hospitalization, clinical data will be collected on enteral feeding (start time, duration, starting dose, feeding type and total enteral feeding time); parenteral nutrition (start time and duration); antibiotics use in infants (type, start time, duration and dose); NEC, LOS and mortality; and respiratory support.

We hypothesize that OAC would regulate gut microbiota and its metabolites in very preterm infants, resulting in an increase in microbial diversity, with increasing dominance of Lactobacillus/Bifidobacterium predominating and a relative decrease in Proteus species. Stool samples will be collected from selected subjects at the first defecation, as well as on the 7th, 14th, 21st and 28th days and immediately frozen at − 80 °C. Fecal samples refrigerated with dry ice will be transported to the Microbiology Research Institute of Shenzhen People’s hospital. After extracting DNA from frozen fecal samples, 16S rRNA gene will be amplified by polymerase chain reaction (PCR) (v3-v4 hypervariable region) and sequenced using Illumina miseq platform. All data collection procedures will be performed following the local coronavirus disease 2019 (COVID-19) epidemic prevention and control policy.

